### 2.4. Sample size

The expected difference in height change was set to 0.45 cm.^[14]^ Based on this, the difference between groups was tripled and set at 1.35 cm. The standard deviation (σ) was set to 2.0, which is the standard for growth disorders (less than −2.0 standard deviation from the average of children of the same age and sex). Accordingly, the sample size was calculated using a 2-tailed 5% significance level, 80% power, and a 1:1 allocation. Accordingly, the required number of subjects per group is 35 and the total number of enrolled subjects is 100 (50 in each group), allowing for a 30% withdrawal rate.

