### 2.8. Random assignment

During subject enrollment, the investigator will assign a unique identification code to each subject in the order of enrollment. Participants who meet the inclusion criteria will be assigned a randomized number according to the randomization plan. The randomization table is a sequential application of the permutations of random numbers (random numbers of A or B) generated by the random number generation program of the safety assessment set system, starting from subject number 1. This was designed and generated in advance by an independent statistician using safety assessment set V9.4 before clinical research. As children and adolescents in the growth and development stages are targeted, they will be divided into four stratified groups and randomly assigned to each group (Table 1).

**Table 1 T1:** Stratification of study subjects considering growth phase characteristics (gender and age)

Girls		Boys	
Group 1	Age between 3 and 9	Group 3	Age between 3 and 10
Group 2	Age between 9 and 12	Group 4	Age between 10 and 12

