### 2.10. Statistical analyses

In this study, analysis will be performed by defining the analysis group as safety, full analysis set (FAS), and per-protocol set analysis. The safety analysis group will be defined as all subjects who have been randomized and who have consumed at least 1 study food and will be evaluated for safety. The FAS analysis group refers to subjects for whom data on primary outcomes can be obtained among those who have taken research food at least once. The per protocol set analysis group includes subjects who have completed the study without serious violations (violation of inclusion and exclusion criteria, use of concomitant medications that are not permitted, and medication adherence less than 70%) according to the research protocol among subjects included in the FAS analysis group. If missing data occurs during FAS analysis or if a subject drops out before the clinical study is terminated, data analysis will be performed with the most recently obtained data as if it were obtained at that time (Last Observation Carried Forward Method).

Statistical analysis is intended to test whether there is a statistical difference between the test and control groups. Therefore, the mean, standard deviation, median, minimum, and maximum values of the outcome measurements will be calculated, and comparisons between the groups will be performed using a 2-sample t-test (Wilcoxon’s rank sum test when the assumption of normality distribution is not satisfied). For laboratory tests and vital sign results, a paired t-test will be used to analyze whether there will be a difference in the amount of change within the group at the end of administration of the test substance compared with before treatment (screening). Further, PAH will be sub-analyzed according to calculation methods such as the VunoMed, TW, and growth chart methods. Additionally, covariate analysis (analysis of covariance; ANCOVA) with stratification as a covariate and subgroup analysis for each stratification will be conducted.

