Among the secondary outcome items, hormone-related items including IGF-1, IGFBP-3, and estradiol levels will be also evaluated. IGF and IGFBP-3 are major indicators for measuring the effect of growth hormones on peripheral tissues and are frequently used indicators in studies confirming the effect of growth. IGF-1 is a hormone that functions as a major mediator of GH-stimulated somatic growth, as well as a mediator of GH-independent anabolic responses in many cells and tissues.^[22]^ IGF-1 is synthesized in the liver and is secreted into the blood under the control of GH. Further, a major function of IGFBP is to transport IGF, which controls access to the extravascular space, as well as tissue localization and distribution. IGFBP-3 is the most abundant form in plasma, with the highest affinity for IGF-1, and is in a saturated state.^[23]^ Estradiol is an estrogen steroid hormone and a major female sex hormone. Additionally, it has important effects on many other tissues, including fat, skin, liver, and the brain, especially estradiol, which has a profound effect on bone. Further, lack of estradiol would result in delayed epiphyseal.^[24]^ By examining the level of estradiol, we also wanted to confirm that antler extract does not interfere with female hormone levels and causes precocious puberty or other hormone-related symptoms.

A limitation of this study is that the stratification will proceed after receiving the study participants without considering the number of participants by age or gender. Further, as the study progresses, the age or sex might influence and bias the results. However, this conforms with the aim of this study, which is to examine the growth effect of antler extract for all children aged 3 to 12 years. Accordingly, additional research should be conducted to compare the growth effects according to age or sex.

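### Randomisation is stratified by sex and age, but the main between-group test ignores the strata; the stratum-adjusted ANCOVA already planned should be the primary analysis

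*Protocol article*

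**What the plan says.** Section 2.8 of the protocol article explains that the children are at different stages of growth and development, so "they will be divided into four stratified groups and randomly assigned to each group". Table 1 defines the groups: girls split at age 9, boys at age 10.

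For the outcome measures, section 2.10 states that "comparisons between the groups will be performed using a 2-sample t-test", replaced by Wilcoxon's rank sum test where normality is not satisfied. The section ends: "Additionally, covariate analysis (analysis of covariance; ANCOVA) with stratification as a covariate and subgroup analysis for each stratification will be conducted". No sentence ranks the ANCOVA above the t-test or calls it primary.

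Section 2.4 sizes the trial for a plain two-group comparison of height change, with no allowance for the strata. The Discussion accepts that the strata may matter: "as the study progresses, the age or sex might influence and bias the results".

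**The concern.** Stratified allocation with balance inside each stratum keeps chance differences in sex and age out of the treatment estimate. A two-sample t-test still counts the between-stratum variance in its error term. The standard error is then larger than the true sampling variability of the estimate: the interval is too wide, the test rejects too rarely under the null, and power is lost against a test that uses the strata.

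The protocol stratifies because growth differs by sex and age, so it expects the strata to predict the outcome. The analysis that matches this design is already written down, but in second place. If the t-test and the ANCOVA disagree, the order of the text favours the less efficient one.

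**Working it through.** **Inputs from section 2.4.** Error rate, power and allocation: "2-tailed 5% significance level, 80% power, and a 1:1 allocation". Effect: "the difference between groups was tripled and set at 1.35 cm". Spread: "The standard deviation (σ) was set to 2.0". The result is 35 per group, raised to 50 per group (100 in total) for 30% withdrawal.

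**Assumptions not in the document.** R², the share of variance in height change explained by the four strata, is taken as 0.10 to 0.34. The total SD is held at 2.0. Strata are of equal size in the simulation below.

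**1. Reproduce the plan's figure.**
- n = 2 × (1.960 + 0.842)² × (2.0/1.35)² = 34.5, so 35 per group.
- 35/0.70 = 50 per group, 100 in total.
- Power at 35 per group is 80.6% by the normal approximation and 79.5% by the exact t calculation, which needs 35.4, so 36 per group.

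The stated size is reproduced, and it is the size for the unadjusted test.

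**2. Standard errors, 35 per group.**
- Used by the t-test: SE = 2.0 × √(2/35) = 0.478 cm.
- True SE under balance within strata: 0.478 × √(1 − R²).
- The t-test's interval is too wide by a factor of 1/√(1 − R²): 1.05 at R² = 0.10 and 1.23 at R² = 0.34.

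**3. Error rate and power under balance within strata (normal approximation).**
- True type I error of the t-test = 2 × [1 − Φ(1.96/√(1 − R²))].
- Power of the t-test = Φ[(1.35/0.478 − 1.96)/√(1 − R²)].
- Power of the adjusted test = Φ[1.35/(0.478 × √(1 − R²)) − 1.96].

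Worked at R² = 0.20, where √(1 − R²) = 0.894:
- Type I error: 1.96/0.894 = 2.19, giving 2.8%.
- t-test power: (2.824 − 1.960)/0.894 = 0.966, giving 83.3%.
- Adjusted power: 1.35/0.428 − 1.96 = 1.197, giving 88.4%.

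| R² (assumed) | t-test type I error | t-test power | Adjusted power |
|---|---|---|---|
| 0 | 5.0% | 80.6% | 80.6% |
| 0.10 | 3.9% | 81.9% | 84.5% |
| 0.20 | 2.8% | 83.3% | 88.4% |
| 0.34 | 1.6% | 85.6% | 93.5% |

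**4. Simulation, 36 per arm, same effect and SD.**

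| R² (assumed) | t-test type I error | t-test power | ANCOVA power |
|---|---|---|---|
| 0.10 | 4.0% | 81% | 84% |
| 0.20 | 2.7% | 83% | 88% |
| 0.34 | 1.4% | 85% | 94% |

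The type I error of the ANCOVA stays at about 5% throughout.

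**5. Same simulation without balance within strata.** The t-test's type I error is near 5%. Its power is 79% to 81%, against 81% to 93% for ANCOVA.

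**6. If the strata explain nothing.** In a separate simulation with 70 children analysed and R² = 0, power was 79.2% for the t-test and 78.6% for ANCOVA. Adjusting costs almost nothing even then.

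**7. The normality check.** Choosing between t and Wilcoxon by a Shapiro-Wilk pre-test (35 per group, unstratified) gave type I error of 5.3% for normal data and 5.2% for exponential data. The check itself does not distort the error rate; ignoring the strata does.

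No step includes baseline height, so any gain from adding it is not counted here.

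**The case against.** The strongest reply is that the remedy is already in the plan. Section 2.10 prespecifies the stratum-adjusted ANCOVA, so only the rank of two planned analyses is in dispute. This is true, and it keeps the point modest. A condensed article may also leave the full covariate list and any interaction test to the analysis plan, so their absence is no fault. What stands is that the article itself puts the unadjusted test first.

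Second, the type I error shortfall needs balance within strata. Section 2.8 gives no block size and describes a table applied in sequence from subject number 1. The Discussion says stratification follows intake without regard to numbers by age or sex. This objection also stands: without such balance the t-test's type I error is about 5%. The power advantage of ANCOVA remains.

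Four stronger readings are tempting, and the document supports none of them:
- A reader might infer that the trial is underpowered. On its own inputs it is not: 35 per group was computed for the unadjusted test, whose power stays at about 80% or above.
- A reader might infer that false positives are inflated. The error runs the other way.
- A reader might infer that a switch to Wilcoxon leaves no effect in cm. Section 2.10 reports means, SDs and medians whichever test is used, and the ANCOVA gives a difference in cm.
- A reader might infer that testing four strata separately inflates the trial's false-positive risk. Nothing makes these subgroup analyses confirmatory, and the Discussion leaves comparisons by age or sex to further research.

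**Conclusion.** The point holds as a matter of efficiency and of matching the analysis to the design. With balance within strata and an assumed R² of 0.10 to 0.34, the t-test runs at a true type I error of about 4.0% to 1.4% instead of 5%, and gives up roughly 3 to 9 percentage points of power (81% to 85% against 84% to 94%). The consequence is an over-wide interval and a conservative test, not an unsafe claim of benefit.

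The size depends on R², which the document does not give, and on the total SD of 2.0. R² = 0 would remove the difference, but the protocol's own reasons for stratifying make that implausible. The type I error figures also depend on balance within strata; the direction of the power advantage does not. This should be changed, but it does not threaten the validity of the trial.

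**What to change.** In section 2.10, name one primary analysis: ANCOVA of the 12-week change in height with treatment, the four randomisation strata and baseline height. Report the adjusted difference in cm with its 95% CI. List the two-sample t-test and the Wilcoxon test as sensitivity analyses, with no normality check deciding which result counts.

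The cost is one paragraph of wording. Stratum is known at randomisation and section 2.9.1 already measures height at baseline, so no new data and no extra children are needed. The sample size can stay as it is.

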**Figure 2. F2:**
[figure not shown]
Schedule of enrollment, intervention, and assessments. (a) Height, weight, and waist and hip circumference. (b) Hematologic and Serum Chemistry test, Urine test, Hormone test, Estradiol. * Researchers will record the dining pattern of the day before using the 24-h recall method. Additionally, researchers will withdraw and check the dietary questionnaire handed out during the previous visit. ** If there was an examination within 4 weeks, it can be used.

If it is determined that the number of study participants does not meet the expectations, changes or additions to the recruitment method will be implemented through discussion between the research sponsor, the person in charge, and the practitioner.

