### 2.12. Adverse events

An adverse event refers to all harmful and unintended signs (including signs and abnormalities in laboratory test results), symptoms, or diseases that occurred in subjects who have received the tested food. These adverse reactions do not necessarily have a causal relationship with the tested food and might include abnormal test results, clinically significant symptoms or signs, changes in physical examination results, hypersensitivity, and progression or worsening of existing diseases.

All serious adverse events occurring during the clinical study period, whether related to the tested food or not, should be reported to the sponsor within 24 hour of the investigator’s awareness, regardless of administration. Adverse reactions occurring up to 28 days after the last administration of the tested food, after the end of the clinical study, should be reported only if they are serious and related to the tested food.

If a suspected unexpected serious adverse reaction (SUSAR) has occurred, the principal investigator should report it to the IRB, to decide whether the study should be continued or discontinued, and report it to the Minister of Food and Drug Safety promptly within the period specified in each of the following items through the sponsor:

- SUSAR that causes death or threatens life must be reported to the Minister of Food and Drug Safety as soon as possible through telephone, fax, or documents within seven days of the first report or knowledge of the sponsor, and a complete report additional reports must be made within 15 days of the date of first knowledge.- All other SUSAR should be reported as soon as possible within 15 days from the date the sponsor receives or becomes aware of the fact.

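### The one test named for laboratory and vital-sign results is a within-group test of mean change, which makes no placebo comparison and is insensitive to a few severely abnormal children

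*Protocol article*

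**What the plan says.** All of the following is in the protocol article.

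- **Test.** Section 2.10 states: "For laboratory tests and vital sign results, a paired t-test will be used to analyze whether there will be a difference". The change tested is "within the group at the end of administration of the test substance compared with before treatment (screening"). The statistic (mean change), the two time points and the within-group setting are therefore all fixed.
- **Aim.** The same section says: "Statistical analysis is intended to test whether there is a statistical difference between the test and control groups". The two-sample t-test (or rank-sum test) and the descriptive summaries are attached to the outcome measurements: "the mean, standard deviation, median, minimum, and maximum values of the outcome measurements will be calculated". Section 2.9 lists growth measures and hormones as outcomes. It does not list haematology, chemistry, urine or vital signs.
- **Safety set.** It comprises "all subjects who have been randomized and who have consumed at least 1 study food and will be evaluated for safety".
- **Laboratory panel.** The Figure 2 caption lists "Hematologic and Serum Chemistry test, Urine test, Hormone test, Estradiol". Section 2.9 states week-6 blood sampling for the hormones. Visit timing for the other tests is in the figure, which is not shown.
- **Adverse events.** The definition in section 2.12 covers abnormal laboratory findings ("including signs and abnormalities in laboratory test results"), and the abstract says that adverse events will be evaluated.

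**The concern.** Safety is a stated aim, and the participants are healthy children aged 3 to 12. The sentence on laboratory and vital-sign data has two weaknesses.

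First, a within-group change over 12 weeks in growing children cannot be attributed to the product without the placebo arm beside it. The sentence does not set the arms side by side, although the section's stated aim is a comparison of test and control.

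Second, the test addresses a shift of the mean. If the extract markedly disturbed a laboratory value in two or three children and left the rest alone, the test would usually be non-significant. A report built on it could then say that no significant laboratory change was seen.

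**Working it through.** **The plan's own figure.** The per-arm size sets n for the check. With a difference of 1.35 cm, SD 2.0, two-sided 5% and 80% power (section 2.4):

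n = 2 × (1.96 + 0.84)² × 2.0² / 1.35² ≈ 34.4, rounded up to 35 per group; 35 / (1 − 0.30) = 50 per group.

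This reproduces the stated 35 and 50. The check uses both, as the arm before and after the planned withdrawal.

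**Limiting case.** Suppose k of n children have the same rise D and the others do not change at all.

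- Mean change = kD/n
- Sample variance = D² × k(n − k) / [n(n − 1)]
- t = mean / √(variance/n) = √[k(n − 1)/(n − k)]

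D cancels, so the size of the abnormality has no effect on t.

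| n | k | t | two-sided p |
|---|---|---|---|
| 50 | 1 | √(49/49) = 1.00 | 0.32 |
| 50 | 2 | √(98/48) = 1.43 | 0.16 |
| 50 | 3 | √(147/47) = 1.77 | 0.083 |
| 50 | 4 | √(196/46) = 2.06 | 0.044 |
| 35 | 3 | √(102/32) = 1.79 | 0.083 |
| 35 | 4 | √(136/31) = 2.09 | 0.044 |

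In this idealised case significance first appears at four children. It is a limit, because real data have background variation.

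**With background variation.** Changes were simulated as normal with SD 1, and k children were given an added shift. The shifts and k are assumptions, since the documents give no laboratory SD or event rate. Share of 40,000 runs with p < 0.05 in one arm:

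| n | k | shift 3 SD | shift 5 SD | shift 8 SD |
|---|---|---|---|---|
| 50 | 0 | about 5% | about 5% | about 5% |
| 50 | 1 | 4.8% | 4.8% | 3.3% |
| 50 | 2 | 7.4% | 8.5% | 7.5% |
| 50 | 3 | 12.1% | 16.4% | 18.1% |
| 35 | 1 | 5.0% | 4.2% | 2.6% |
| 35 | 2 | 8.2% | 8.4% | 6.2% |
| 35 | 3 | 13.9% | 17.6% | 17.5% |

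**A more extreme assumption.** With SD 6 and outliers of +120, a shift of 120/6 = 20 SD, n = 50 and 20,000 runs, the paired test rejects in 5.1% of runs with no affected child. It rejects in 0.1%, 0.7% and 9.5% with one, two and three. One or two very severe cases therefore make a significant result less likely than none.

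**Would a placebo comparison of means cure this?** In the same 20 SD case, a between-arm t-test rejects in 0.9%, 3.0% and 15.8% of runs for one, two and three affected children. The missing placebo comparison and the insensitivity to outliers are thus separate weaknesses.

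**Time points.** Only screening and the end of dosing ("at the end of administration of the test substance compared with before treatment (screening") enter the test. Whatever intermediate sample exists is not part of it.

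**The case against.** The strongest objection is that the protocol has another route to individual abnormalities. Under section 2.12 an abnormal laboratory result is an adverse event, and every randomised child who took study food is in the safety set. Out-of-range counts, shift tables and listings are also commonly left to a full protocol or analysis plan, neither of which is shown.

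The first part stands. A reader might infer that laboratory safety is judged only by the t-test, and the documents do not support that. The second part stands for absence alone, so missing tables are not the point here. The point is the test that section 2.10 does fix, which is poorly matched to its purpose.

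Four further inferences also go beyond the text:

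- **Early withdrawals are left out.** No passage says so. The end of administration could be each child's last dosing visit. The carry-forward rule is worded around the full analysis set, so its reach to safety data is unclear.
- **Week-6 safety samples are discarded.** Week-6 sampling is stated only for hormones. The caption groups the other tests with them, but their timing cannot be confirmed.
- **The t-test is wrongly applied to graded urine results.** This depends on a reporting format that the text does not give.
- **The test can never detect a few outliers.** With background variation it rejects in roughly 10% to 18% of runs at three affected children. It is insensitive, not blind.

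Minimum and maximum values are promised for outcome measurements. Even if extended to safety data, they would show the most extreme value but not how many children were affected.

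**Conclusion.** The concern holds in limited form. The only test that section 2.10 names for laboratory and vital-sign results is a within-group test of mean change from screening to the end of dosing. It does not compare the extract with placebo, and it does not use any intermediate sample. With 1 to 3 affected children among 35 to 50, it was significant in under about 20% of runs in every scenario tried, against 5% with none affected, and sometimes in fewer than 5%.

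These rates rest on assumed normal background changes and assumed shifts of 3 to 20 SD, because the documents supply no laboratory variability. Individual abnormal results can still surface as adverse events, so the defect lies in what the named laboratory analysis would show by arm. It is not a failure to record harm. The sample size is unaffected.

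**What to change.** In section 2.10:

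1. Report mean change in laboratory and vital-sign values by arm, as description only.
2. Make the main laboratory and vital-sign safety summary a count per arm, in the safety set. Count children who move from normal at screening to out of range or clinically significant at any post-baseline sample collected, including any week-6 or withdrawal sample.
3. Give an exact 95% confidence interval for each arm and list the affected children's values. For example, 3 of 50 would read 6%, interval 1.3% to 16.5%.
4. Tabulate in the same way any result that is reported as grades.

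The cost is a wording change and one set of tables from data already collected, with no change to the 100 children. The downside is that the counts are descriptive and carry no significance test.

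### For safety laboratory tests and vital signs the only test named is a within-group paired t-test, which leaves the randomised placebo arm unused

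*Protocol article*

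**What the plan says.** Section 2.10 of the protocol article opens its account of the tests with a between-group purpose: "Statistical analysis is intended to test whether there is a statistical difference between the test and control groups". For the outcome measurements it follows through: "comparisons between the groups will be performed using a 2-sample t-test", with a rank-sum test as the non-normal alternative.

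A separate rule then covers laboratory and vital-sign results: "a paired t-test will be used to analyze whether there will be a difference in the amount of change within the group". The change runs from the screening value to the end of administration. No between-group test is named for these variables. The section later adds an ANCOVA adjusting for stratum and subgroup analyses by stratum, without saying which endpoints they apply to.

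Two other places bear on the scope of the paired rule. The Figure 2 legend lists, under one footnote, "Hematologic and Serum Chemistry test, Urine test, Hormone test, Estradiol". Section 2.9.2.6, under the heading for secondary outcomes, covers human growth hormone, IGF-1, IGFBP-3, their ratio and estradiol. The Discussion also treats the hormones as secondary outcomes, and says of estradiol that "we also wanted to confirm that antler extract does not interfere with female hormone levels".

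**The concern.** The trial randomises against placebo so that whatever happens to all children over 12 weeks can be subtracted. The paired rule does not make that subtraction. Participants are 3 to 12 years old and growing, so a mean change from screening in the active arm can arise with no product effect. Section 2.6 also excludes children for abnormal laboratory tests, and the paired test uses screening as its reference. Regression to the mean is therefore plausible for any variable on which children were selected.

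The error runs both ways. A shared drift can appear as a product effect. A real product effect opposite to the drift can cancel it, leaving a within-arm change near zero. Setting the two arms' p-values side by side does not help, because one significant and one non-significant result is not a test of the difference between them. At stake is how laboratory and vital-sign safety is read for a product given to children.

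**Working it through.** **1. The plan's own figure.** Section 2.4 gives a difference of 1.35 cm, SD 2.0, two-sided 5%, 80% power and 1:1 allocation. 
n per group = 2 × (1.960 + 0.842)² × (2.0/1.35)² ≈ 2 × 7.85 × 2.195 ≈ 34.5, so 35. 
With 30% withdrawal: 35/(1 − 0.30) = 50 per group. 
Both stated figures reproduce. They concern height and are used here only as arm sizes: 35 (completers) and 50 (all enrolled).

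**2. What each test estimates.** Let δ be the drift common to both arms and τ the product effect.
- Active-arm change: δ + τ
- Placebo-arm change: δ
- Between-group difference: (δ + τ) − δ = τ

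The paired test in the active arm tests δ + τ = 0. The two-sample test of change tests τ = 0. If τ = −δ, the expected active-arm change is zero and the paired test rejects only 5% of the time, although the effect is real.

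**3. Size under no product effect (τ = 0).** The article gives no drift for any laboratory value or vital sign, so d = δ/(SD of individual change) is an assumption, shown over a range. The probability p that the active-arm paired test is significant comes from the noncentral t distribution with n − 1 degrees of freedom and noncentrality d√n, two-sided 5%. The chance that the active arm is significant and placebo is not is p(1 − p), since the arms are independent.

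| Assumed drift d | p, n = 35 | p, n = 50 | Active significant, placebo not, n = 35 |
|---|---|---|---|
| 0 | 0.050 | 0.050 | 0.048 |
| 0.1 | 0.089 | 0.107 | 0.081 |
| 0.2 | 0.210 | 0.284 | 0.166 |
| 0.3 | 0.407 | 0.548 | 0.241 |
| 0.4 | 0.633 | 0.792 | 0.232 |
| 0.5 | 0.820 | 0.934 | 0.148 |
| 0.8 | 0.996 | 1.000 | 0.004 |

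Example: d = 0.3 and n = 35 give noncentrality 0.3 × √35 = 1.77 and p = 0.407; then 0.407 × 0.593 = 0.241. The last column cannot exceed 0.25, the maximum of p(1 − p), reached at p = 0.5.

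**4. The between-group test on the same data.** In 20,000 simulated trials with 35 per arm, the two-sample t-test of change was significant in 5.0%, 5.1% and 5.1% at d = 0, 0.3 and 0.5. The paired test in the active arm gave 5.0%, 41.4% and 82.4%, in line with the table.

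**5. Which rule covers the hormones.** Section 2.9.2.6 and the Discussion make them secondary outcomes, so the between-group sentence in section 2.10 reaches them. The Figure 2 legend lists them beside haematology, chemistry and urine, so the paired sentence can be read to reach them too. Nothing says which governs.

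**The case against.** The best defence is that section 2.10 does not call the paired test the only analysis. The between-group aim comes first, and the paired test could be an addition to it. A full protocol or SAP may hold more. Safety also does not depend on these p-values alone: section 2.12 counts abnormal laboratory results as adverse events whatever their cause, and a safety population is defined. This limits the consequence, but it does not remove the point. The article does not merely omit a between-group test for these variables; it names a different one. The ANCOVA does not close the gap, because its endpoints are not named.

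The drift sizes are also assumed. That is correct. With zero drift the paired test holds its 5%, and the table shows how quickly this is lost.

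Four stronger readings are tempting and are not supported:
- A reader might infer that the hormones will be judged by paired tests alone. They are listed as secondary outcomes, which are compared between groups. The legend is a visit schedule, not an analysis rule, and creates at most an ambiguity.
- A reader might infer that boys and girls will be pooled for estradiol. Table 1 defines the strata by sex and age, and analyses by stratum are planned.
- A reader might infer that a non-significant result will be taken as proof of no interference with female hormones. The Discussion gives this as a reason for measuring estradiol and states no such decision rule.
- A reader might use imprecision for estradiol as the measure of the defect. With an assumed 25 girls per arm, the 95% half-width is 2.01 × √(2/25) = 0.57 SD. That figure describes a two-sample comparison and says nothing about the paired test. It supports only reporting an interval.

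**Conclusion.** The point holds for safety laboratory tests and vital signs. The one test named for them is within-group, contrary to the section's own aim, and it cannot separate a product effect from maturation, time or regression to the mean. With 35 per arm, no product effect and an assumed common drift of 0.3 to 0.5 SD of change, the active-arm test is significant in about 41% to 82% of trials, against about 5% for the between-group test. A pattern of active significant and placebo not would arise in up to about 25% of null comparisons.

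This rests on reading the paired rule as applied to each arm separately, on equal drift and SD in both arms, and on roughly normal changes. For the hormones, including estradiol, the finding is only that two rules could apply and the text should say which does. The primary height analysis is not affected. The change should be made, but it does not threaten the trial's main result.

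**What to change.** In section 2.10 and in the SAP:
- For every continuous laboratory and vital-sign variable, name a between-group analysis: either ANCOVA of the week-12 value on treatment, stratum and the pre-treatment value, or a two-sample comparison of change. Report the difference with its 95% confidence interval.
- Keep within-group tests descriptive at most, and draw no conclusion about the product from them.
- State that human growth hormone, IGF-1, IGFBP-3, their ratio and estradiol, as secondary outcomes, are governed by the between-group analysis despite their place in the Figure 2 legend.
- Base any statement about estradiol on the interval for the between-group difference, and not on a non-significant p-value.

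The cost is a few sentences and a small amount of programming. The paired analysis already needs the pre-treatment and end-of-treatment values, so no extra visit, sample or participant is required.
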